### Study objectives and endpoints

The primary objective is to evaluate the efficacy of adjuvant nonavalent HPV vaccination in women who will undergo treatment for (histologically proven) vHSIL in preventing clinical recurrence of vHSIL up to 24 months.

The second objectives are:The effectiveness (complete remission) after treatment in patients receiving vaccination versus placebo at 6 and 12 months.Complete remission after treatment in patients receiving vaccination versus placebo at 6 and 12 months in primary episode (newly diagnosed) vHSIL versus recurrence.The effectiveness of adjuvant vaccination in different treatments of vHSIL (laser, imiquimod, excision) after 24 months.Additional treatment for vHSIL needed in the study period, and differences between the study groups.The effect of vaccination versus placebo on different hrHPV types (HPV type of primary and recurrence).The difference in immune response to HPV vaccination versus placebo vaccination. (We use HPV antibodies as a surrogate marker for immune response. Peripheral blood mononuclear cells (PBMCs) are bio banked for the possibility to measure in-depth cellular immune response at the molecular level at the end of the trial).Cost-effectiveness (IMTA Medical Consumption Questionnaire (iMCQ) and IMTA Productivity Cost Questionnaire (iPCQ) will be used).Quality of life (measured by Euroqol 5D-5L questionnaire) and sexual health (measured by Female Sexual Function Index, FSFI questionnaire) improved after vaccination compared to placebo.The effect of vaccination versus placebo on CIN/cervical cytology of the uterine Cervix.Long-term follow-up: The difference between HPV vaccination and placebo group in number of recurrences of vHSIL (5 and 10 years) and vulvar malignancies (2,5 and 10 years).

The primary endpoint is a difference in the number and percentage of patients with a clinical recurrence rate of vHSIL between HPV vaccination and placebo up to 24 months post-treatment.

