### Data collection

All data will be collected using an electronic Case Report Form (eCRF) and electronic questionnaires. Data from the eCRF and questionnaires will be collected and stored using Castor EDC. Sequential subject numbers will be assigned to enrolled participants in the study. Access to stored data will be restricted solely to the principal and coordinating investigators of each participating center.

Demographic and baseline disease characteristic data will be summarized for each treatment group and consist of age, parity, cervical cytology and HPV status, prior treatment for vHSIL, prior treatment for cervical HSIL, smoking, and co-morbidities in which we focus on auto-immune diseases and history of cancer.

At each follow-up visit, the following data will be collected: visual/physical examination and preferably photo documentation of the vulva. If there is any suspicion of recurrence of vHSIL, a biopsy will be taken for histology and HPV typing endpoint, cervical cytology, and if additional treatment will be started.

At the start of the study, after 6, 24, and 60 months, patients will be asked to fill out questionnaires.

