### Detailed procedure

Patients with vulvar lesions are referred to the gynecologist according to their regular care. In the case of vHSIL, a biopsy will be taken for histological examination by a pathologist as part of regular care. At that time, potential participants will receive oral and written study information. In the case of histology-proven vHSIL participants will be invited for the screening visit.

In cases of uncertainty about whether a lesion is primary, residual, or recurrent, we have established an independent board of three experts on vulvar diseases to provide a definitive decision by consensus.

During the screening visit, routine cervical cytology (if not previously taken) and HPV status are obtained, along with visual examinations, including photo documentation to monitor lesion progression or regression.

At the follow-up visits, patients will undergo visual and physical examinations, with a preference for photo documentation of the vulva, to monitor any changes or recurrence of lesions or the development of new lesions. In case of suspicion of recurrence or a new lesion, a biopsy is taken. When it is not feasible to take a new biopsy, but new treatment is initiated, this is also considered a clinical recurrence. Quality-of-life questionnaires and immune response analysis will be performed, adhering to guideline-based care.

Recurrence is defined as any reappearance of vHSIL after six months from the start of treatment, while residual disease is defined as the presence of clinical suspicion and preferable histological conformation of vHSIL within six months from the start of the treatment.

In case of uncertainty regarding the histological diagnosis, an expert gynecological pathologist will review the slides digitally.

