### Randomization, stratification, blinding and treatment allocation

Randomization will be performed through the secure web-based interface Castor EDC (Castor Electronic Data Capture available at: https://castoredc.com). Patients will be randomly assigned to either adjuvant HPV vaccination or placebo in a 1:1 ratio. Randomization will be stratified by country of inclusion, treatment group (surgery, laser vaporization, and topical imiquimod), and the first episode of vHSIL versus recurrence. The study team, the local investigator, and the patient are blinded for treatment allocation of the study medication. The allocated medication in the Netherlands will be prepared by the pharmacy at the Erasmus MC and administered to the patient by a designated study team member from Erasmus MC. Study medication will be masked for the administrator of the vaccination and the patient.

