### Sample size calculations

The sample size calculations are based on the available evidence, which describes a recurrence rate of 19% versus 32% in favor of HPV vaccination [5]. With a target power of 0.8 and a two-sided alpha of 0.05, we need a total of 498 patients (249 in each arm), including a loss of follow-up and a 20% correction of the supposed different effect in treating the first episode of vHSIL versus the recurrence of vHSIL.

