### Data analysis

The primary outcome will assess the relative risk of vHSIL recurrence within 24 months, analyzing the efficacy of adjuvant nonavalent HPV vaccination using logistic regression methods adjusted for country of inclusion, treatment types, and primary versus recurrence vHSIL. A 95% confidence interval will be estimated for the odds ratio, with significance determined by a likelihood ratio test. *P*-values below 0.05 will be considered statistically significant.

Analysis of secondary endpoint(s) Secondary objectives 1, 2, 4, 9, and 10 will be analyzed similarly to the primary endpoint, using logistic regression methods adjusted for the stratification variables: country of inclusion, treatment types, and primary versus recurrence vHSIL. 95% Confidence intervals will be estimated for the odds ratios and significance will be determined using likelihood ratio tests. *P*-values below 0.05 will be considered statistically significant.

Secondary objectives where the effectiveness of vaccination is compared between different patient groups (secondary objectives 3 and 5) will be analyzed using logistic regression methods adjusted for stratification variables. 95% Confidence intervals will be estimated for the odds ratio, and significance will be determined using a likelihood ratio test. *P*-values below 0.05 will be considered statistically significant.

Secondary objective 6 will be analyzed using a linear regression model to determine the difference in log-transformed antibody levels at baseline and after placebo or vaccination and adjusted for stratification variables. The impact of change in antibody levels on the primary endpoint will be analyzed using a logistic regression model adjusted for stratification variables. 95% Confidence interval will be estimated for the coefficients, and significance will be determined using a likelihood ratio test. *P*-values below 0.05 will be considered statistically significant.

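### The model for the cervical outcome (secondary objective 9) leaves out baseline cervical status, which the trial collects; adding it costs little and may gain power

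*Protocol article*

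**What the plan says.** The ninth secondary objective in Study objectives and endpoints is "The effect of vaccination versus placebo on CIN/cervical cytology of the uterine Cervix". Data analysis puts it in a shared group: "Secondary objectives 1, 2, 4, 9, and 10 will be analyzed similarly to the primary endpoint, using logistic regression methods adjusted for the stratification variables". The variables are then named as country of inclusion, treatment type, and primary versus recurrent vHSIL. These are the three factors that stratify the randomization, and none describes the cervix.

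Two other sections show that baseline cervical data are gathered. Detailed procedure states: "During the screening visit, routine cervical cytology (if not previously taken) and HPV status are obtained". Data collection lists baseline characteristics that "consist of age, parity, cervical cytology and HPV status, prior treatment for vHSIL, prior treatment for cervical HSIL", among others.

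The exclusion criteria remove women with current invasive carcinoma or a history of HPV-related genital carcinoma. They do not remove women with CIN, abnormal cytology or cervical HPV.

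**The concern.** The primary model suits the primary endpoint. Every woman has vHSIL at entry, so its presence at baseline cannot explain who recurs. The cervix is different. Women can enter with normal or abnormal cytology and with or without cervical HPV, and no randomization stratum balances this. Cervical status at entry probably predicts cervical status later, yet the model carried over from the vulvar endpoint has no term for it.

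The covariates for objective 9 are named, so this is a stated choice and not a gap. The same section uses baseline values where it means to: the antibody analysis (objective 6) refers to levels at baseline and after injection.

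At stake is the precision of the vaccine-versus-placebo comparison on the cervix. A prognostic baseline term would raise power and would correct the estimate for whatever chance imbalance in cervical status the two arms happen to have.

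**Working it through.** **The plan's own figure.** The only sample-size figure concerns the primary endpoint. For "a recurrence rate of 19% versus 32% in favor of HPV vaccination", at two-sided alpha 0.05, power 0.80 and 1:1 allocation:

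n per arm = [1.96 × √(2 × 0.255 × 0.745) + 0.842 × √(0.32 × 0.68 + 0.19 × 0.81)]² / 0.13² ≈ 176.

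The article enlarges this, "including a loss of follow-up and a 20% correction of the supposed different effect", without giving the loss rate. With 15% loss, 176 × 1.2 / 0.85 = 248.5, so 249 per arm and 498 in total. The match depends on that inferred 15%. No event rate, power or sample size is given for objective 9, so what follows rests on assumed rates.

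**Simulation set-up.** Logistic regression with a likelihood ratio test for arm, with and without one binary baseline cervical term.
- Assumed evaluable women: 398 (498 less 20%).
- Assumed control-arm follow-up positivity by baseline status: as in the table.
- Vaccine effect: a common relative risk, set so that power without the term is about 80%.
- Runs: 4,000 per scenario, giving a simulation error of about √(0.8 × 0.2 / 4,000) = 0.6 points for each power figure.
- The stratification terms were left out of both models for simplicity.

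| Control risk, baseline negative vs positive | Baseline OR | Baseline prevalence | Power without term | Power with term |
|---|---|---|---|---|
| 10% vs 10% | 1 | 20% | 82.8% | 82.9% |
| 10% vs 30% | 3.9 | 20% | 81.2% | 82.2% |
| 10% vs 30% | 3.9 | 30% | 82.2% | 83.8% |
| 10% vs 30% | 3.9 | 50% | 81.0% | 83.1% |
| 10% vs 60% | 13.5 | 20% | 82.0% | 88.4% |
| 10% vs 60% | 13.5 | 30% | 79.9% | 88.4% |
| 10% vs 60% | 13.5 | 50% | 80.0% | 88.4% |
| 5% vs 70% | 44 | 50% | 80.1% | 93.8% |

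With no vaccine effect, the rejection rate was 4.8% to 5.6% across the scenarios, with or without the term (2,500 runs each).

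**Second set of assumptions.** Here the conditional odds ratio for vaccine is 0.5 and 50% are baseline positive.
- 10% vs 60%, 249 per arm: power 0.77 without the term and 0.87 with it.
- 10% vs 60%, 199 per arm: 0.66 and 0.78. The gain in points is larger when starting power is lower.
- 15% vs 40%, 249 per arm: a gain of about 1 to 3 points in repeated simulation.

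**Rough cross-check.** If r is the baseline-to-follow-up correlation, linear adjustment multiplies the variance by 1 − r². From 80% power, the new power is Φ(2.80 / √(1 − r²) − 1.96). This gives 0.84 at r = 0.3, 0.90 at r = 0.5 and 0.94 at r = 0.6. In the 10% vs 60% case at 50% prevalence, r = 0.5 × 0.5 / √(0.35 × 0.65) = 0.52. The logistic result there (88.4%) is slightly below the linear approximation.

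**Chance imbalance.** With 50% prevalence and 249 per arm, the difference in baseline prevalence between arms has standard error √(2 × 0.25 / 249) = 4.5 points, so 1.96 standard errors is 8.8 points. Under 10% vs 60%, this shifts follow-up positivity by 8.8 × 0.5 = 4.4 points, for example 37.2% vs 32.8%. With no vaccine effect, the unadjusted odds ratio would then be (0.372 / 0.628) / (0.328 / 0.672) = 1.21, or 0.82 in the other direction.

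**The case against.** **The planned analysis is valid.** Adjusting for the randomization factors reflects the design, and the test holds its level. A reader might infer that an imbalance in cervical status biases the result. It does not: across repetitions the imbalance averages out, and the confidence interval already allows for it. This stands, and it limits the point to efficiency.

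**Baseline may already enter through the endpoint.** The endpoint list describes HPV types in cervical cytology before and after vaccination. A reader might infer that baseline cervical data serve only the baseline table, but that wording contradicts it. If the binary outcome is change or clearance, baseline is partly built in and the simulations do not describe the analysis exactly. The article does not define the binary outcome. However, objective 9 is stated as a between-arm effect on CIN/cytology, and for that outcome the model has no baseline term.

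**The size is unknown.** A reader might infer that baseline status is the strongest predictor, or that every woman has a fresh cervical result at screening. Neither is documented. Cytology is taken only if not already available, so it may be older and less predictive. Detailed procedure does not say that HPV status is cervical. Data collection mentions follow-up cytology in the sentence about suspected recurrence, so the number evaluable is uncertain. If CIN events are few, extra categories could make the model sparse. These points affect the size of the gain and how the term is coded. They do not make the omission preferable.

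**An unseen analysis plan may add covariates.** That is possible, but the article names the covariates for this objective, and any such plan would then differ from the published model.

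**Conclusion.** The point holds as an efficiency weakness in one secondary analysis. The model named for objective 9 omits a collected baseline value that is probably prognostic.

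From a starting power near 80%, the omission costs about 0 to 2 points under weak or moderate prognosis, 6 to 10 points under strong prognosis (10% versus 60%), and about 14 points under very strong prognosis (5% versus 70%). Every one of these rates is assumed, because the documents give none for the cervix. No scenario showed a loss from adding the term beyond simulation error.

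The documents do not support a claim that the analysis is biased or invalid, or that the loss is certain to be large. The primary endpoint is untouched.

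**What to change.** In Data analysis, take objective 9 out of the shared list and give it its own sentence, for example: *Secondary objective 9 will be analysed by logistic regression of follow-up cervical status on randomized arm, adjusted for the stratification variables and for the corresponding baseline cervical status: baseline cytology category for a cytology/CIN outcome, baseline cervical hrHPV status for a cervical HPV outcome.* Keep the planned likelihood ratio test and 95% confidence interval. The binary outcome should be stated alongside, so that the matching baseline variable is unambiguous.

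Specify in advance that cytology categories will be collapsed if events are sparse, and that women without a usable baseline result enter as a separate category, so that none is dropped. Make the change before unblinding, since a covariate added afterwards would look data-driven.

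The cost is one sentence and one model term, with no new visits, samples or patients. There are two small downsides. The odds ratio becomes conditional on baseline status and so is not directly comparable with one that is not. A smear taken well before screening may predict less well, which reduces the gain.

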## Background

Annually, approximately 45,240 women globally are affected by vulvar carcinoma, with a yearly mortality of 15.000 [1]. Around one-third of vulvar cancers arise from a precursor caused by high-risk Human Papilloma Virus (hrHPV), called vulvar High-Grade Squamous Intra-Epithelial Lesion (vHSIL). The standardized incidence rate of vHSIL in Europe is estimated to be approximately 3.3 per 100,000 women years. In the Netherlands, an average of 300 women are newly diagnosed with vHSIL annually. Across Europe, there has been a consistent upward trend in vHSIL incidence over the past two decades, mirroring patterns observed in HPV-related malignancies [1]. The peak incidence of these precancerous vulvar lesions typically occurs between the ages of 35 and 40 [2]. Approximately 10% of women diagnosed with vHSIL, despite undergoing treatment, will progress to develop vulvar cancer within ten years after initial diagnosis. Recurrent vHSIL substantially increases the risk of malignancy [2].

Despite available treatments such as surgery, laser vaporization, and topical imiquimod, vHSIL recurrence rates remain high, affecting at least 30% of treated women within two years, regardless of treatment modality [2, 3]. Unfortunately, effective preventive strategies to address vHSIL recurrence are currently absent.

Promising empirical evidence suggests that HPV vaccination could reduce the risk of vHSIL recurrence. A retrospective secondary analysis of pooled data of two RCTs showed a significant reduction of 35% (irrespective of causal HPV type) to 64% (related to vaccine type) for recurrences of vHSIL and low-grade squamous intraepithelial lesion (LSIL) after adjuvant quadrivalent HPV vaccination [4]. Recently, a case-control study was published showing a reduction of 40% in recurrences after quadrivalent HPV vaccination; due to small groups, this reduction was not significant [5]. There is a notable absence of high-quality studies investigating adjuvant nonavalent vaccination, specifically in women treated for vHSIL.

We propose a prospective, double-blind, randomized controlled trial to evaluate the efficacy of adjuvant nonavalent HPV vaccination compared to placebo in reducing recurrence rates among women currently treated for vHSIL. Given that almost all HPV variants linked to vHSIL are covered by the nonavalent vaccine, this trial seeks to provide a novel preventive strategy for vHSIL recurrence [6–9].

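### Fixed-horizon logistic regression is a poor fit for the 5- and 10-year outcomes, and too heavily adjusted for the roughly 8 to 10 cancers expected by 2 years

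*Protocol article*

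**What the plan says.** The Data analysis section of the protocol article sets logistic regression for 24-month recurrence, adjusted for country, treatment type and first versus recurrent episode. It reports an odds ratio with a 95% interval and a likelihood ratio test. The next paragraph extends that model: "Secondary objectives 1, 2, 4, 9, and 10 will be analyzed similarly to the primary endpoint, using logistic regression methods".

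Under Study objectives and endpoints, the tenth secondary objective is the long-term comparison, described as the "number of recurrences of vHSIL (5 and 10 years) and vulvar malignancies (2,5 and 10 years". Study design provides two years of clinical follow-up within the trial, with later assessment at 5 and 10 years.

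Two other statements bear on the point. Sample size calculations gives the total as "including a loss of follow-up", without a rate. Background says that about 10% of treated women "will progress to develop vulvar cancer within ten years after initial diagnosis".

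**The concern.** Logistic regression on status at a horizon needs each woman's status at that horizon. A woman seen event-free at year 4 and then lost has no 5- or 10-year status. If she is dropped while women who had an event before leaving are kept, the risk is overstated. If she is coded as a non-event, it is understated. Death without cancer raises the same coding question and is a competing event, not a loss. Losses are expected even for the two-year comparison, so incomplete status at 5 and 10 years is foreseeable.

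A separate problem is sparseness. Few cancers can be expected by 2 years, yet the model carries the arm and three adjustment factors.

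At stake are the long-term percentages by arm, the long-term effect estimate if loss differs between arms, and the precision and stability of the 2-year malignancy result.

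**Working it through.** **The plan's own figure.** Sample size calculations uses available evidence "which describes a recurrence rate of 19% versus 32% in favor of HPV vaccination", "With a target power of 0.8 and a two-sided alpha of 0.05", and concludes "we need a total of 498 patients (249 in each arm". With unpooled variances:

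- n per arm = (1.960 + 0.842)² × (0.19×0.81 + 0.32×0.68) / 0.13² = 7.849 × 0.3715 / 0.0169 = 172.5, so 173.
- 173 × 1.2 (stated correction) × 1.2 (assumed 20% loss) = 249.1 per arm, or 498 in total.

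The figure is reproduced, but only by assuming a loss rate, because the article gives none. All loss rates below are assumptions too.

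**Effect of loss on a fixed-horizon risk.** Let p be the true risk at horizon T, with a constant hazard, and let a fraction d have loss times uniform on (0, T).

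- λT = −ln(1 − p).
- Chance that a woman with a loss time has her event first: E = 1 − p/(λT).
- Observed events: O = (1 − d)p + dE.
- Lost counted as non-events: O. Lost dropped: O / [O + (1 − d)(1 − p)].

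Ten-year cancer, p = 0.10: λT = 0.1054 and E = 0.0509.

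| Assumed loss d | O (lost = non-event) | Lost dropped |
|---|---|---|
| 30% | 0.070 + 0.0153 = 8.5% | 0.0853 / (0.0853 + 0.630) = 11.9% |
| 50% | 0.050 + 0.0254 = 7.5% | 0.0754 / (0.0754 + 0.450) = 14.4% |

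**Effect estimate, equal loss.** Take 10% versus 6% (illustrative RR 0.6; true OR 0.574) with 50% loss in both arms. The OR is 0.573 (dropped) or 0.580 (non-event). It hardly moves.

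**Effect estimate, unequal loss.** Suppose no vaccine effect, 10% in both arms, and loss of 30% vaccine and 50% placebo. From the table, the RR is 0.1192/0.1436 = 0.83 (dropped) or 0.0853/0.0754 = 1.13 (non-event); the OR is 0.81 or 1.14. The truth is 1, and the two codings err in opposite directions.

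**The 24-month primary endpoint, for comparison.** With 15% loss in both arms, 32% becomes 34.0% or 29.8%. The OR goes from 0.498 to 0.497 or 0.505. With loss of 20% vaccine and 10% placebo, the RR goes from 0.594 to 0.63 or 0.56. At 20% loss in both arms, power is about 88% for the complete-case comparison and 90% for a time-to-event analysis (hazard ratio 0.546).

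**Expected cancers.** A constant hazard from 10% in ten years gives a risk of 1 − 0.9^(t/10) at year t. The counts below ignore loss.

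| Year | Risk | Events in 498, no effect | Events if RR 0.6 | Power if RR 0.6 |
|---|---|---|---|---|
| 2 | 2.1% | 10.4 | 249 × 0.0209 × 1.6 = 8.3 | about 11% |
| 5 | 5.1% | 25.6 | 20.4 | about 21% |
| 10 | 10% | 49.8 | 39.8 | about 38% |

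**Is the 2-year model estimable?** With K countries it has 1 (intercept) + 1 (arm) + 2 (modality) + 1 (episode) + (K − 1) coefficients, so seven for K = 3.

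- Chance that an arm has no cancer, with no loss: about 2 × (1 − 0.0209)^249 = 1% if RR is 1. If RR is 0.6 it is (1 − 0.0209)^249 + (1 − 0.0125)^249, about 5%.
- Simulated full model (3 countries at 60/25/15%, modality 40/35/25%, episode 60/40%, RR 0.6, 448 women, all assumed): arm OR finite in 93% of trials, likelihood ratio statistic finite in all, at least one covariate coefficient infinite in 54%.
- Some factor level without any cancer, at 10% loss: 18–29% of trials with 1 country, 41–56% with 3, 87–92% with 5.

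Precision, for 3 versus 5 cancers in 249 per arm: OR = (3/246)/(5/244) = 0.60, SE of the log OR = √(1/3 + 1/246 + 1/5 + 1/244) = 0.736, 95% interval 0.14 to 2.52.

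**The case against.** The strongest reply is that the handling of lost women is a missing-outcome rule, which a full protocol or SAP normally sets. Logistic regression with multiple imputation or weighting can use partial follow-up, so dropping and counting as event-free are not the only choices. This stands: the absence of such a rule here is not a finding. What remains is that the article does fix the model for objective 10, and that model needs an added device to do what a time-to-event analysis does directly.

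Second, the planned estimate is an odds ratio, which hardly moves under equal loss, and nothing in a double-blind trial points to unequal loss. This also stands. But the endpoints are stated as numbers and percentages of patients, and those do shift under equal loss.

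Third, a binary model suits the primary endpoint, which is the percentage with recurrence up to 24 months and was sized as two proportions. I accept this. A reader might infer that the primary analysis should be replaced; the small shift in the odds ratio and the two-point power difference do not support that.

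Fourth, a reader might infer from the high chance of an empty factor level that the 2-year cancer model is mostly not estimable. That confuses covariate terms with the vaccine term. When a country has no cancers its own coefficient diverges, but the vaccine odds ratio and its test remain. Nor does the sparseness come from loss: it comes from few events and several covariates, and a Cox model with the same covariates would share it.

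**Conclusion.** The point holds for objective 10, in two separate parts.

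1. At 5 and 10 years, the model named has no direct place for event-free partial follow-up. A 10% ten-year cancer risk could be reported anywhere from 8.5% to 11.9% at 30% loss, or from 7.5% to 14.4% at 50%, depending on coding alone. The effect estimate is affected materially only if loss differs by arm. These sizes rest on a constant hazard, evenly spread loss and assumed loss rates.
2. By 2 years, about 8 to 10 cancers are too few for the adjusted model. The vaccine odds ratio would usually exist but say very little, and covariate coefficients would often be infinite. This rests on a constant hazard and on assumed numbers and shares of countries, modalities and episodes, none of which the article gives.

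It does not follow that the 24-month logistic regression is wrong, or that the 2-year malignancy comparison cannot be computed. This is a worthwhile improvement to a secondary objective and does not threaten the primary conclusion.

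**What to change.** Change the analysis wording for objective 10:

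- For recurrence at 5 and 10 years and malignancy at 5 and 10 years, estimate cumulative incidence by arm with death as a competing event. Compare arms with a Cox model stratified or adjusted for the randomisation factors, pooling small countries and using Firth's penalty if events are sparse.
- For malignancy at 2 years, report counts by arm with exact intervals and no adjusted model.
- Keep logistic regression as the primary 24-month analysis. Add a sensitivity analysis that estimates 24-month risk from time to first recurrence in visit intervals. Count recurrence from six months after the start of treatment, as Detailed procedure defines it, and state how women with residual disease before then are handled.

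The cost is mainly wording and a little more analysis. Event, death and last-contact dates are needed. Data collection lists findings at each visit but does not mention dates, so their capture should be confirmed, above all for long-term follow-up. Recurrence dates are known only to the interval between visits, which a visit-interval model accommodates; at 5 and 10 years, wide contact intervals would limit how finely timing can be resolved.

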The secondary endpoints are:Difference in the number and percentage of patients with a clinical recurrence rate of vHSIL between HPV vaccination and placebo at 6 and 12 months.Difference in the number and percentage of patients with a clinical recurrence rate of vHSIL between HPV vaccination and placebo at 6 and 12 months for primary vHSIL versus recurrent vHSIL.Difference in the number and percentage of patients with a clinical recurrence rate of vHSIL between the different treatment modalities.Difference in number and percentage for additional treatment necessary after primary treatment.Description and percentage of different hrHPV types. Percentage clearance of primary HPV type for vaccination versus placebo.Concentration of HPV antibodies and percentage of increase or decrease after vaccination.Is there a correlation between the number or percentage of recurrence? Is that different in primary versus recurrence episodes of vHSIL.Incremental cost-effectiveness ratio (ICER) describes the difference in costs and budget impact analysis.Description and change in numeric value and percentage in different score forms questionnaires. Percentage increase of decreased quality of life, sexual impact, and productivity impact.Difference in number and percentage of HPV types in cervical cytology and vHSIL before and after vaccination.Difference in number and percentage in the recurrence rate of vHSIL and vulvar cancer between HPV vaccination and placebo. Other HPV-related diseases known?

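### The model for the cervical objective omits the baseline cervical status that the trial plans to collect: a valid analysis, but possibly less efficient than it could be

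*Protocol article*

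**What the plan says.** All references are to the protocol article.

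- **Objective.** Study objectives and endpoints, ninth secondary objective: "The effect of vaccination versus placebo on CIN/cervical cytology of the uterine Cervix".
- **Endpoint.** The matching secondary endpoint is worded differently: "Difference in number and percentage of HPV types in cervical cytology and vHSIL before and after vaccination".
- **Model.** Data analysis groups objective 9 with others that "9, and 10 will be analyzed similarly to the primary endpoint, using logistic regression methods adjusted for the stratification variables". It then names the three variables: country of inclusion, treatment type, and primary versus recurrent vHSIL.
- **Randomisation.** "Randomization will be stratified by country of inclusion, treatment group (surgery, laser vaporization, and topical imiquimod), and the first episode of vHSIL versus recurrence". Cervical status is not a stratification factor, so it is balanced only by chance.
- **Baseline data.** Detailed procedure: "During the screening visit, routine cervical cytology (if not previously taken) and HPV status are obtained". Data collection lists, among baseline characteristics, "age, parity, cervical cytology and HPV status, prior treatment for vHSIL, prior treatment for cervical HSIL".
- **Follow-up data.** Cervical cytology appears in a sentence that opens with suspicion of recurrence: "a biopsy will be taken for histology and HPV typing endpoint, cervical cytology, and if additional treatment will be started".

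**The concern.** The model was written for vulvar recurrence and carried over to an outcome in another organ. Some of the cervical abnormality or HPV found at follow-up may be persistence of what was there at entry. If so, the baseline value of the outcome is probably its strongest predictor, and leaving it out leaves explainable variation in the comparison.

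The covariates are named in the text, so this is a stated choice and not a detail deferred to an analysis plan. What is at stake is precision and power for one secondary objective. The test's validity and the trial's primary conclusion are not affected.

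**Working it through.** **1. The plan's own figure.** The only sample size is for vHSIL recurrence: 32% versus 19%, power 0.8, two-sided alpha 0.05. The two-proportion formula gives 176 per arm. With the stated 20% correction and an assumed 15% loss to follow-up (the rate is not stated), 176 × 1.2 / 0.85 = 248.5, which rounds up to the stated 249 per arm. This says nothing about objective 9, for which no event rate, effect size or power is given. Every cervical input below is therefore an assumption.

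**2. Approximation.** Let R² be the share of outcome variance explained by baseline cervical status. Then

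power after adjustment ≈ Φ((z_base + 1.96)/√(1 − R²) − 1.96),

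where z_base is the normal quantile of the power without adjustment. Example with base power 60% and R² = 0.15: (0.253 + 1.96)/0.922 − 1.96 = 0.44, and Φ(0.44) = 67%, a gain of 7 points. Gains in points:

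| Base power | R² 0.05 | 0.10 | 0.15 | 0.20 | 0.30 |
|---|---|---|---|---|---|
| 30% | 1.3 | 2.8 | 4.4 | 6.1 | 10.4 |
| 50% | 2.0 | 4.2 | 6.6 | 9.1 | 14.9 |
| 60% | 2.2 | 4.5 | 7.0 | 9.7 | 15.3 |
| 70% | 2.2 | 4.5 | 6.9 | 9.3 | 14.4 |
| 80% | 2.0 | 4.0 | 6.0 | 7.9 | 11.8 |
| 90% | 1.4 | 2.7 | 4.0 | 5.2 | 7.2 |

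**3. Simulation at full trial size.** 498 women, 1:1, likelihood ratio test in logistic regression with stratification-type covariates, with and without one binary baseline covariate. Base power was about 65%, control-arm events 10–30%, and 30–50% were positive at baseline.

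| Odds ratio, baseline to outcome | Gain (points) |
|---|---|
| 3 | about 0 to 3 |
| 5 | 2 to 6 |
| 10 | 4 to 11 |
| 20 | 6 to 18 |

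Two more extreme settings went slightly beyond this: about 20 points (40% events, odds ratio 20) and 21 points (30% events, odds ratio 30). With 5% control-arm events and a treatment odds ratio of 0.5, base power was about 30% and the gain about 0 to 2 points whatever the baseline odds ratio.

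**4. Simulation with losses.** 211 evaluable women per arm (249 × 0.85) and a vaccine odds ratio of 0.5 in all women.

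- *Strong persistence:* 30–50% positive at baseline; placebo follow-up abnormality 45–60% in those women and 5–8% in the others. Power rose from 64% to 72%, 59% to 74%, 66% to 75%, 50% to 61% and 54% to 69%.
- *Weaker persistence:* R² = π(1 − π)(q₁ − q₀)² / [p(1 − p)], with π the share positive at baseline, q₁ and q₀ the follow-up rates in baseline positives and negatives, and p the overall rate.

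| π | q₁ vs q₀ | R² | Power without → with baseline |
|---|---|---|---|
| 20% | 30% vs 5% | 0.11 | 41% → 44% |
| 10% | 30% vs 5% | 0.08 | 32% → 35% |
| 20% | 20% vs 5% | 0.05 | 36% → 38% |
| 30% | 30% vs 10% | 0.06 | 60% → 63% |
| 20% | 40% vs 15% | 0.06 | 68% → 70% |

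With no vaccine effect, the adjusted test rejected in 4.8% of runs.

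**5. Chance imbalance.** With 40% positive at baseline, the between-arm difference has standard error √(2 × 0.4 × 0.6/211) = 4.8 points. If follow-up abnormality is 50% versus 6% by baseline status, an imbalance of one standard error shifts the observed difference by 4.8 × 0.44 = 2.1 points. The effect itself under an odds ratio of 0.5 is 23.6% − 15.2% = 8.4 points.

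**The case against.** The strongest reply is that adjusting for the stratification factors is a valid analysis that holds its type I error, and that objective 9 is an unpowered secondary question on which no main conclusion depends. That stands, and it makes the point minor.

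The size of the gain also depends on favourable inputs. A reader might infer that the trial gives up 7 to 15 points of power. The documents do not support this: they contain no cervical prevalence, persistence or effect figure, and weaker persistence gives only 2 to 3 points. Nor does the vaccine necessarily act on abnormality already present. If the odds ratio is 0.3 in baseline-negative women and 1.0 in the rest (30–40% positive), power is 12–17% without adjustment and 15–21% with it, so the covariate would not rescue the objective.

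Other stronger readings also fail:

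- Chance imbalance is random error that the test and interval already allow for. It is not bias.
- The covariates are not all vulvar, since country is among them.
- Baseline collection is the screening plan. Completeness is not stated, cytology may be an earlier result, and the text does not say outright that the HPV status is cervical.

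Finally, it is fair to say that the outcome must be settled first, because the objective names CIN/cytology and the endpoint names HPV types. That shapes the fix but does not remove the point: the endpoint's before-and-after wording itself calls on a baseline value for which the model has no place.

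**Conclusion.** The point holds in a limited form. The stated covariate list for objective 9 omits a baseline measurement that is already planned and likely to be prognostic. The analysis is valid but may be less efficient than it could be.

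The gain from adjustment is about 0 to 18 points of power over the assumed range. About 7 to 15 points requires baseline status to explain roughly 15–30% of outcome variance together with base power of about 50–70%. For an outcome near 5%, as CIN might be, it is close to nil. No single figure can be derived from the documents. Severity is minor.

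**What to change.** In Data analysis, for objective 9 and before unblinding:

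1. Align the objective with its endpoint, so that it is clear whether the binary outcome is a CIN/cytology result or an HPV result.
2. Prespecify the baseline value of that same outcome (cytology result, hrHPV status, or both) as a covariate alongside the three stratification variables.
3. Give missing baselines a not-available category.

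No new data are needed. The costs are a few degrees of freedom, a rule for missing baselines, and an odds ratio that is conditional on baseline cervical status and should be reported as such.
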